**Method:**

SMART-AGE examines the effect of an app-based multilevel treatment designed to enhance social participation, physical fitness, and health awareness. The target population comprises healthy and community-dwelling adults 67 years and older with basic digital skills in two socially diverse communities. Treatment relies on an Android-based tablet computer, on which three apps offering interventions in the core areas of social participation, physical fitness, and health awareness are pre-installed. A feedback app designed to provide participants with a feedback option at any time is also offered. Participants are randomly assigned to three intervention arms and assessed at baseline and after 3 and 6 months. Arm 1 receives the full intervention, consisting of the social participation app, the physical fitness app, the health awareness app, and the feedback app. The health awareness app is available in months 4 to 6, meaning that participants receive the full three-app intervention only in the second half of the intervention period. Arm 2 receives the social participation app and the feedback app throughout the intervention. Arm 3 serves as an active control condition in that a stand-alone tablet with a low-dose introduction to publicly available standard apps is provided. The data protocol includes assessment of three primary outcome domains: social support and loneliness, motor capacity and physical performance, and health awareness and health locus of control. Potential moderators (e.g., cognitive function, depression) as well as various technology-oriented constructs (e.g., skills, acceptance) are also assessed. App use data are automatically collected across the full intervention interval in arms 1 and 2. Data management is conducted within a cloud-based REDCap architecture. Feedback recordings via the feedback app are collected in arms 1 and 2 and undergo qualitative analysis.

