## Objectives

According to our preregistration (see below), objectives of the SMART-AGE trial are as follows: Can the regular use of the offered apps (1) prevent or reduce loneliness and promote social support (particularly smartVERNETZT), (2) improve motor capacity (particularly KOKU), (3) increase health self-awareness and health-related control beliefs (particularly smartIMPULS), and (4) increase technology-related skills and the acceptance of technology?

To address these objectives, we decided for an intervention scheme as follows: a full intervention group (IG), a partial IG, and an active control group (CG). An active CG was installed to ensure that observed effects can be attributed to app use and not simply to the provision of a tablet to the participants coming with some social attention. In the full intervention condition, the participants will have access to all of the SMART-AGE specific apps, namely smartVERNETZT, KOKU, smartIMPULS, and smartFEEDBACK. In the partial intervention condition, the participants will have access to two SMART-AGE specific apps, namely smartVERNETZT (containing all standard apps) and smartFEEDBACK. This arm allows us to investigate the impact of the smartVERNETZT app without the co-use of other apps that also aim to improve the quality of life. It also serves as a most direct comparison to the previous PRISM trial [6]. Participants in the active CG will just be given the device and receive a basic introduction to publicly available and pre-installed standard apps (e.g., calendar app, e-mail app). In all of the three treatment arms, participants will receive a tablet and be given a short introduction on how to use a tablet in general.

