### Participant timeline

Home-based assessments take place at the time of study enrollment (T1) and after 6 months (T6). In addition, a brief online self-assessment will be conducted 3 months after study enrollment (T3). At the beginning of the first home visit (HV; day 1 in T1), participants are informed about data protection, can ask open questions, and get general information about the study. Then they are provided with a tablet, a corresponding manual, and are instructed on how to use the tablet in a short training session. At that moment, the tablet is switched to “study mode,” enabling the monitoring of app usage data of the participants from that point forward. Afterwards the online-assessments are explained and set up on the tablet. Then the home-based assessments take place including cognitive and motoric measurements. During the motor capacity assessment, the body-fixed movement sensor is placed on the participant’s lower back.

One week after the initial HV, the randomization has already taken place, and a second HV is conducted for participants of all groups. During this visit, the tablets are modified allowing participants in both IGs (arms 1 and 2) access to two SMART-AGE specific apps: smartVERNETZT and smartFEEDBACK. These groups also receive instructions and a manual on how to use these new apps. Participants in the CG (arm 3) are given access to the standard applications on the tablet. However, detailed explanations are only given for the video chat tool. The documents containing information about the SPs, completed and signed during the HVs, as well as the data sheets of the cognitive test battery, are securely stored in a locked cabinet in SMART-AGE designated office spaces. Four to 6 weeks after the second HV, participants in the full IG additionally receive access to and are instructed in the use of the KOKU app. Approximately 10 days after the digital assessment at 3 months, the participants of the full IG are introduced to the smartIMPULS app during HV IV.

In order to counterbalance potential social activation effects, 25% of participants in study arms 2 and 3 (active CG and the partial IG) were randomly selected to receive one additional video calls. Randomization was performed using the R package “blockrand” [39].

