### Blinding

Participants are always aware of the study arm they are assigned to, as they either have access to none, two, or all four of the project apps, except during the baseline assessment. To gather data, two HVs, HV I and HV V, are conducted. It is crucial that the researchers conducting these visits remain blinded to the participants’ group assignments. To facilitate this, the research team is divided into two distinct groups: assessors and app-instructors. The assessors are responsible for data collection during HV I and HV V, while the app-instructors handle HV I, II, III, and IV. The initial HV occurs prior to the randomization of participants, allowing both assessors and instructors to be involved in this stage of the study. We do not anticipate any requirement for unblinding the assessors, but if required, the project coordinators will have access to group allocations and any unblinding will be reported. The randomization list used to allocate participants to the study arms was created by the lead study statistician and the project coordination team, who are the only ones with access to the data file containing personalized information. After individuals are screened positive, the project coordination allocates them to the randomly selected study arm using a study management software. The software allows the information of the allocated study arms to be hidden from blinded assessors while showing it to user groups who need this information.

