### Statistical methods

Our main hypotheses will be tested using multilevel and structural equation models, following an intention-to-treat analysis. We will test the effect of experimental group on primary outcomes separately for each outcome with a 3 × 3 factorial design multilevel model with the between-subjects factor *study arm* (active CG vs. partial IG vs. full IG) and the within-subjects factors *study time point* (study start vs. 3 months vs. 6 months), followed by post-hoc comparisons controlling for the family-wise error rate. Models will include random intercepts for each participant and their place of residence. As covariates, we will consider participants’ gender, their age, and their frequency and intensity of app usage. We plan to report all analyses with and without the inclusion of these covariates. Where the assessment of primary outcomes is only possible during HVs, we will remove the 3-months level from the within-subjects factor *study time point*.

In addition, we will test the effect of experimental groups on primary outcomes first separately for each outcome and then jointly for all four primary outcomes using latent change models. In these models, the multilevel structure of the data will be accounted for by multigroup comparisons to examine whether (a) the effects of the two IGs are larger than the effects of the active CG (see hypotheses), whether (b) the effects of the full IG are larger than the effects of the partial IG (see hypotheses), and (c) by which individual and/or sociodemographic variables the effects of the two interventions on the four primary outcome variables are moderated.

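### App usage, which arises after randomisation and is set by arm, is listed as a covariate in the intention-to-treat models, and neither the adjusted nor the unadjusted version is named confirmatory

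*Protocol article*

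**What the plan says.** Under Statistical methods, the Protocol article states: "Our main hypotheses will be tested using multilevel and structural equation models, following an intention-to-treat analysis". Each primary outcome gets a multilevel model with arm (three levels), time point (start, 3 months, 6 months) and random intercepts for participant and place of residence. The covariates to be considered are "gender, their age, and their frequency and intensity of app usage". The rule for reporting is: "We plan to report all analyses with and without the inclusion of these covariates". The section does not say which version carries the confirmatory test, or whether usage enters as one value per person, as a value per time point, or in interaction with time.

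Other sections fix what usage is:
- **Timing.** The project apps are opened at the second home visit. Participant timeline: "One week after the initial HV, the randomization has already taken place".
- **Dependence on arm.** Under Blinding, participants know their arm because "they either have access to none, two, or all four of the project apps".
- **Role.** Under Objectives: "An active CG was installed to ensure that observed effects can be attributed to app use".
- **Where it is recorded.** Abstract, Method: "App use data are automatically collected across the full intervention interval in arms 1 and 2". Participant timeline, on the tablet's study mode set at the first home visit: "enabling the monitoring of app usage data of the participants from that point forward", with no limit to any arm.

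**The concern.** A covariate in a randomised comparison should be fixed before allocation or be unaffected by it. Usage of the project apps is neither. It follows allocation, its possible range is set by the arm, and it is the mechanism that the trial wants to detect. Holding it constant asks what the arms would do if they did not differ in use, which is not the question that the hypotheses pose. It also brings in confounding, because within an intervention arm people who use the apps more may differ from others in motivation or health.

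If the apps work through being used, the two promised versions should be expected to disagree under some codings. The article then offers two answers to each main hypothesis and no rule for choosing between them. Usage is also grouped with age and gender, so as written the usage-free version drops those two baseline variables as well.

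**Working it through.** **1. Does the effect of adjustment depend on how usage is coded?** Baseline is a level of the time factor, so the treatment effect is the arm-by-time interaction, that is, a difference between arms in change.

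- *Time-constant main effect.* A term γU for each person is the same at baseline and at 6 months. In the change it gives γU − γU = 0, so the interaction is untouched. A small simulation (240 per arm, three time points, control usage 0, coefficient of variation about 0.7, whole effect through usage, 8 runs) gave 0.329 with and without usage, SE 0.077 in both. With 10% dropout it gave 0.314 in both, differing by at most 0.003.
- *Time-varying from 0 at baseline, or interacting with time.* The change now contains γU, and usage competes directly with arm. In the same simulation the interaction fell to about −0.05 (SE 0.11). A separate two-time-point simulation (60 runs) took it from 0.285 to 0.00, with the SE rising from 0.072 to 0.102, a factor of 1.42. A change-score or endpoint model behaves in the same way.

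The article does not say which coding applies. The Outcomes section does plan to analyse usage metrics over time, so a time-varying coding is plausible.

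**2. Size of the bias when usage competes with arm.** The documents give no usage distribution, so these inputs are assumptions: control usage 0; intervention usage with mean m = 1 and SD s = 0.4; correlation 0.5 with a motivation trait; outcome SD 1. The true effect d = 0.28 is borrowed from the social-support result of the earlier PRISM trial cited in the article. It is not a design input.

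Adjusted arm coefficient = d − m × (within-arm slope of outcome on usage). The slope is (share of effect through usage) × d/m + c × 0.5/s, where c is the trait's effect on the outcome. A two-arm least-squares simulation (240 per arm, 2,000 runs) agrees:

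| Share through usage | c | Formula | Simulated | Rejection rate, without → with usage |
|---|---|---|---|---|
| 0 | 0 | 0.28 | 0.28 | 0.87 → 0.32 |
| 0.5 | 0 | 0.28 − 0.14 = 0.14 | 0.14 | 0.86 → 0.12 |
| 1 | 0 | 0.28 − 0.28 = 0 | 0.00 | 0.86 → 0.055 |
| 0 | 0.2 | 0.28 − 0.25 = 0.03 | 0.03 | 0.86 → 0.05 |
| 1 | 0.4 | 0.28 − 0.28 − 0.50 = −0.50 | −0.50 | 0.85 → 0.77, now with the wrong sign |

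In the first row there is no bias and the whole cost is precision.

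**3. Precision.** For two equal arms with control usage 0, the squared correlation of arm with usage is (m²/4)/(m²/4 + s²/2).
- Coefficient of variation 0.7: 0.25/(0.25 + 0.245) = 0.505; variance inflation 1/(1 − 0.505) = 2.02; SE × √2.02 = 1.42.
- Coefficient of variation 0.4: 0.25/(0.25 + 0.08) = 0.758; variance inflation 4.13; SE × 2.03 (simulated 2.04).

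**4. Control arm.** On the Abstract's statement, control usage of the project apps is either structurally zero or unobserved. If it is zero, the arm term extrapolates to intervention participants who never used the apps. If it is unobserved, full information maximum likelihood has to extrapolate usage into an arm where it is never seen. On the Participant timeline's statement, some tablet-level usage may exist for controls, but it would measure something other than project-app use.

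**5. Sample size.** 128 × 5 = 640; 640/0.90 gives 712; the next multiple of 72 is 720. The published figure is reproduced, and dropping usage from the models gives no reason to change it.

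**The case against.** The strongest reply is that the article already protects itself. A version without the covariates is promised for every analysis, the covariates are only to be considered, and under the simplest coding the treatment term does not move. All of this stands. A reader might infer that adjustment for usage removes the intervention effect from the trial's results. The documents do not support that, because a usage-free estimate will be reported and the loss depends on a coding that the article does not state.

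Three further inferences also go too far:
- *Usage is not recorded in controls.* The Abstract points that way, but the Participant timeline describes monitoring without an arm limit.
- *The whole control arm, 240 of 720, would be lost.* That needs listwise deletion, whereas the article specifies full information maximum likelihood in all models.
- *Half of the main analyses are affected.* The covariate list belongs to the multilevel models. The latent change models are described separately without a usage covariate, and only a broad reading of the reporting sentence brings them in.

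It can also be said that naming the confirmatory version and the coding is work for an analysis plan, which is not shown, and that a comparison without age and gender is still valid. Both are fair. Place of residence stays in as a random intercept in either version, and adding age and gender mainly affects precision. But the article does not leave the covariate open. It names usage for the models labelled intention-to-treat, and that choice is wrong under any coding: harmful under some, pointless under the other.

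**Conclusion.** The point holds and should be fixed, but it does not invalidate the trial. App usage is a post-randomisation variable on the intended causal path and does not belong among the covariates of the confirmatory models. The usage-adjusted contrast is not an intention-to-treat effect, and the article gives no rule for which version decides the hypotheses.

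The size is conditional. With usage time-varying from 0, interacting with time, or in a change or endpoint model, an effect of 0.28 can become anything from 0.28 with a larger SE, through 0, to −0.50 under the assumptions shown. The SE rises about 1.4-fold at a usage coefficient of variation of 0.7 and about 2-fold at 0.4, with control usage 0. With usage as a time-constant main effect, the arm-by-time term is essentially unchanged. The usage distribution, its link to motivation and the effect size are all assumed, because the article gives none of them for this trial.

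**What to change.** 1. Delete frequency and intensity of app usage from the covariates of all confirmatory models.
2. Name as primary the arm-by-time model with place of residence, age (or age group) and gender, and without usage.
3. Report usage only in analyses labelled exploratory, such as dose-response within arms 1 and 2 or mediation. The Outcomes and Discussion sections already plan to relate usage to change in outcomes, so nothing of interest is lost.
4. Reconcile the Abstract (usage data in arms 1 and 2) with the Participant timeline (monitoring without an arm limit), and state what, if anything, is recorded in controls.

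The cost is wording in the analysis plan and moving any usage-adjusted tables to the exploratory part. No data collection changes, and the sample size stays at 720.

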### Outcomes

There are four primary outcome domains in this study that will be compared across all three study arms:Health-related self-awareness, control beliefs, and self-efficacy, which includes measures like the Health Locus of Control Scale [48], Health Literacy [49], Adapted Health Consciousness Scale [50], and Self-efficacy [51];Motor capacity and performance, which includes measures like the Timed Up and Go Test [52] and movement sensor-based physical activity parameters (e.g., steps per day) using Axivity AX6 sensors;Loneliness and social support, which includes measures like the UCLA Loneliness Scale [53], Lubben Social Network Scale [54].Technology acceptance, competence, and usage, which includes measures like Computer Anxiety [55] and End User Frustration [56].

Another important part of the assessment architecture in SMART-AGE is the generation of multiple usage data while the apps are used by study partners. This includes, for instance, the assessment of weekly usage frequency and intensity (e.g., total time spent using the apps, number of interactions within the apps), as well as the analysis of app-specific features used—such as whether video calling was utilized in smartVERNETZT, how many training levels were completed in KOKU, or how many questions were answered in smartIMPULS or smartFEEDBACK. These metrics will be analyzed over time and across multiple apps to identify usage patterns and dynamics, which can then be related to changes in the targeted outcomes.

A complete list of all assessments, encompassing all measures related to the main and secondary hypotheses, as well as demographic measures that describe the sample is provided in Appendix Part 2. In addition, we also collect objective user data from the SMART-AGE apps to evaluate in more detail the app usage.

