For all statistical tests, we will use alpha = 0.05 as the threshold for statistical significance. Post-hoc comparisons will be controlled for the family-wise error rate. We will be reporting standardized effect sizes and confidence intervals whenever possible. In addition, we will evaluate the goodness-of-fit of SEMs based on the comparative fit index [CFI; [59]] and the root mean square error of approximation [RMSEA; [39]] and compare model fits with the Akaike Information Criterion [AIC; [60]] and the likelihood ratio test. Following the recommendations by Browne and Cudeck [58] and Hu and Bentler [61], we consider CFI values > 0.90 and RMSEA values < 0.08 to indicate acceptable model fit and CFI values > 0.95 and RMSEA values < 0.06 to indicate good model fit. AIC differences ≥ 10 will be interpreted to indicate a substantial advantage in relative model fit in direct model comparisons [62]. We will assess the statistical significance of model parameters with the two-sided critical ratio test. To our knowledge, this is the first study to systematically monitor and evaluate long-term app usage in a German sample of older adults. We therefore lack the necessary prior knowledge to determine exclusion criteria for app usage and engagement with the tablet. Thus, a blinded analyst [63] will screen study partners’ app usage after the data is collected to propose appropriate criteria. The blinded analyst will not have access to the outcome variables, protecting the confirmatory nature of the statistical inference.

Outlier values in measured variables (assessments) will be removed if they exceed ± 3 SD of the sample mean of their respective study arm and study time point. In addition, we will exclude individuals whose responses appear random (e.g., identical responses to all questions). Physical activity data will only be included if the individual has worn the sensor for at least 4 days.

The type of missing data will be assessed and accounted for using the full information maximum likelihood method in all statistical models. If data are found to be Not Missing at Random, this will be addressed appropriately to minimize potential bias and stated as a limitation.

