## Discussion

Robust evidence on the use of digital technology as a prevention means to strengthen multiple resources important to maintain QoL in old age is lacking. In terms of strengths, SMART-AGE first aims to improve this situation based on a complex trial design and a multimodal intervention by means of four interconnected apps. Target areas include enhancing social participation, increasing physical activity, and boosting health awareness, as well as the intensive collection of feedback, while using the respective apps.

Second, the exploitation of expected data including user-centered feedback and objective usage information may hold the potential for important insights. For example, effects observed at the primary outcome level (loneliness and social support, motor capacity and performance, health-related self-awareness and health control beliefs, technology acceptance and competence) can be linked with the objective app usage patterns and user feedback. This enables a deeper understanding of why and how the interventions work or do not work, and for whom.

Third, SMART-AGE also follows a multilevel approach of self-report data, performance-based data, and tracking data for assessing primary outcome domains. Therefore, possible differential effects of interventions on subjective versus objective assessment levels can be tested.

Fourth, SMART-AGE allows for examining short-term (3 months) and medium/long-term (6 months) effects of app use. Given the short cycles of technology and product innovation, we posit that 6 months is a sufficient time period for robust effect testing. For example, SMART-AGE’s digital appliances do not use speech control features, but it can be expected that speech control and speech assistance will much expand also in the area of digital preventive tools, e.g. [64].

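### Moderation analyses run at an unadjusted 0.05 with no exploratory label, so a chance moderator may be reported as a significant result

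*Protocol article*

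**What the plan says.** All passages are in the protocol article.

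- **Statistical methods, opening sentence:** "Our main hypotheses will be tested using multilevel and structural equation models, following an intention-to-treat analysis". The latent change models are among these.
- **Statistical methods, latent change models:** three questions are put in one sentence. Contrast (a) sets the two intervention groups against the active control, and contrast (b) sets the full intervention against the partial one. Both refer back to the hypotheses in parentheses. The third has no such reference: "c) by which individual and/or sociodemographic variables the effects of the two interventions on the four primary outcome variables are moderated".
- **Statistical methods, error rate:** "For all statistical tests, we will use alpha = 0.05 as the threshold for statistical significance". The next sentence reads "Post-hoc comparisons will be controlled for the family-wise error rate". The preceding paragraph mentions post-hoc comparisons only as the follow-up to the 3 × 3 multilevel model.
- **Statistical methods, parameters:** "We will assess the statistical significance of model parameters with the two-sided critical ratio test".
- **Outcomes:** "There are four primary outcome domains in this study that will be compared across all three study arms".
- **Abstract, Method:** "Potential moderators (e.g., cognitive function, depression) as well as various technology-oriented constructs" are assessed. Two moderators are named, as examples only.
- **Objectives:** none of the four hypotheses concerns moderation. The dose–response analysis there is called exploratory, as is the use of momentary assessment data in the Discussion. Moderation is not.

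**The concern.** The issue is a rule the article states, not a detail left to another document. One threshold of 0.05 covers every test, and the only multiplicity control is attached to another class of comparison. Item (c) asks about two interventions, four outcomes and an open set of variables, within the same models that carry the main contrasts.

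Read literally, any moderator term below 0.05 may be reported as significant. Nothing tells the reader that it came from an unadjusted search. Because the authors do use the word exploratory elsewhere, its absence here leaves the status of these results unclear. At stake is how far the trial may claim that an intervention works better in some groups than in others. The primary contrasts and the sample size are not affected.

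**Working it through.** **The plan's own figure.** The article gives no error rate for the moderation family. The only stated figure is 0.05 per test. The check therefore asks what that implies for the family.

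**Inputs from the article**
- Alpha per test: 0.05, two-sided for model parameters (Statistical methods).
- Interventions: 2. Primary outcomes: 4 (Statistical methods, Outcomes).

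**Assumptions, because the article gives no figure**
- Number of moderators m: 2 to 5. Two is the number named as examples. Five would be those two plus age, gender and place of residence.
- Form of test: either one omnibus test per moderator, or one test per moderator, outcome and intervention.
- No true moderation.

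**Formula.** For k independent tests, P(at least one false positive) = 1 − 0.95^k.

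**Case 1, one omnibus test per moderator (k = m)**
- m = 2: 1 − 0.95² = 0.0975, about 0.10.
- m = 5: 1 − 0.95⁵ = 0.226, about 0.23.

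Positive correlation between the tests lowers these values towards 0.05. They reach 0.05 only if the tests are perfectly correlated. With m = 1 there is no inflation.

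**Case 2, one test per outcome and intervention (k = 4 × 2 × m = 8m)**
- m = 2: k = 16, and 1 − 0.95¹⁶ = 0.56.
- m = 5: k = 40, and 1 − 0.95⁴⁰ = 0.87.

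These tests will be correlated. Simulation with equally correlated normal test statistics (100,000 draws) gives:

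| Moderators | Tests | Correlation 0 | 0.5 | 0.8 |
|---|---|---|---|---|
| 2 | 16 | 0.56 | 0.38 | 0.21 |
| 5 | 40 | 0.87 | 0.57 | 0.28 |

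A second simulation used a more specific structure: 0.5 between the two intervention contrasts (shared control), 0 to 0.7 between outcomes and 0 to 0.5 between moderators. It gave 0.38 to 0.53 for two moderators and 0.63 to 0.85 for five, inside the range above.

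The expected number of false positives does not depend on correlation. It is 0.05 × 16 = 0.8 for two moderators and 0.05 × 40 = 2.0 for five.

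**Does the stated control reach item (c)?** The multilevel paragraph attaches family-wise control to comparisons that follow the arm-by-time model. Item (c) belongs to the latent change models in the next paragraph. The later general sentence again says only post-hoc comparisons. On the plain reading, moderator terms fall under the 0.05 rule and outside the control.

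**The case against.** The case on the other side has real force.

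- **The text already sets (c) apart.** It lacks the reference to the hypotheses that (a) and (b) carry, and it asks by which variables rather than whether. A reader might infer that moderation is planned as a confirmatory subgroup test. The article does not say so, and its wording leans the other way. What stands is that the status is left to inference while a significance threshold is stated.
- **The number and form of tests are assumed.** A reader might infer that a false moderator is more likely than not. That holds in only part of the range: it fails throughout Case 1, at correlation 0.5 with two moderators (0.38) and at correlation 0.8 with five (0.28). The article also names likelihood ratio tests and an AIC difference of at least 10 for model comparisons. For one extra parameter, that AIC rule needs a chi-square of 10 + 2 = 12 (p about 0.0005), so a decision on AIC alone would not be inflated. But the article does not assign (c) to AIC, and the 0.05 rule covers every test.
- **The general sentence on post-hoc comparisons might cover subgroup comparisons.** This reading is possible but not stated, and the preceding paragraph points to the multilevel model.
- **Other documents may fix the moderators.** The appendix, the preregistration or an analysis plan may list them and state their status. For that reason the open list is not itself the point. The point rests on the stated error rule.
- **The Discussion does not turn (c) into a claim.** It says "This enables a deeper understanding of why and how the interventions work or do not work, and for whom". A reader might take this as announcing subgroup conclusions from item (c), or as a step towards offering the apps to particular groups. In context it concerns linking outcome effects to app usage and user feedback, and the dissemination plans mention no subgroup targeting. Neither inference is supported.

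**Conclusion.** The point holds in a limited form. Item (c) examines moderation of two interventions on four outcomes under an unadjusted 0.05, outside the stated family-wise control and without an exploratory label. For tests at that threshold, the chance of at least one false moderator exceeds 0.05 for any count of two or more. With 2 to 5 moderators it is about 0.10 to 0.23 (omnibus tests, independent) or about 0.21 to 0.87 (one test per outcome and intervention, correlation 0.8 down to 0). These figures rest on an assumed moderator count, an assumed form of test and no true moderation. They support a correction to how moderation results may be reported. They do not show that a false finding is likely in every case, and they do not touch the primary contrasts. The change is worth making because it limits what the trial may conclude and costs almost nothing.

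**What to change.** In Statistical methods, state that item (c) is exploratory. Exempt it from the unadjusted 0.05 rule: report moderator-by-arm estimates with 95% confidence intervals and make no claim of significance. The article already commits to confidence intervals where possible, so little else changes.

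If any moderation claim is meant as confirmatory, limit it to the stratification factors named under Recruitment (age group, gender, place of residence) and apply Holm across those tests at 0.05. With one test per factor, outcome and intervention there are 3 × 4 × 2 = 24 tests, so the smallest p-value would be compared with 0.05/24 = 0.0021. With one omnibus test per factor it would be compared with 0.05/3 = 0.017.

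The cost is a label or one adjustment step, with no new data and no change to the sample size. The downside is that moderator results can no longer be called significant at an unadjusted 0.05. The Discussion sentence needs no change.
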